## Abstract

**Background::**

The sensitivity and specificity of the routine detection of acute myocardial infarction (AMI) in early diagnosis are not high, which can not meet the clinical needs. Copeptin combined with hypersensitive cardiac troponin T (hs-cTnT) is a new detection scheme, and its value in the early diagnosis of acute myocardial infarction is still unclear. Accordingly, the aim of this study is to evaluate the diagnostic value of copeptin combined with hypersensitive troponin T detection in early acute myocardial infarction.

**Methods::**

This is a prospective, randomized; double-blind diagnostic trial to investigate the diagnostic value of copeptin combined with hypersensitive troponin T detection in early acute myocardial infarction. Approved by the clinical research ethics of our hospital. Patients were randomly divided into one of 2 test protocols: (A) copeptin combined with hs-cTnT group and (B) cardiac troponin I (cTnI) group. Patients, doctors, nurses, inspectors, and data-gathering assistants were blinded to group allocation. We will focus on the sensitivity comparison of the 2 detection methods at different time periods and the sensitivity and specificity comparison of the two detection methods. Data were analyzed using the statistical software package SPSS version 25.0 (Chicago, IL).

**Discussion::**

The purpose of this study is to evaluate the diagnostic value of copeptin combined with hypersensitive cardiac troponin T detection in early acute myocardial infarction. The results of this study will establish clinical evidence for the detection of high sensitivity cardiac troponin T in the early diagnosis of acute myocardial infarction.

**Ethics and dissemination::**

Private information from individuals will not be published. This systematic review also does not involve endangering participant rights. Ethical approval was not required. The results may be published in a peer-reviewed journal or disseminated at relevant conferences.

**OSF Registration number::**

DOI 10.17605/OSF.IO/6TE5Z.

## Introduction

1

Acute myocardial infarction (AMI) is an acute coronary syndrome in which blocked coronary artery causes insufficient blood supply to the heart muscle and impairs heart function, has the characteristics of rapid progression and high mortality,^[1]^ is the leading cause of cardiovascular death worldwide.^[2]^ Rapid and accurate early diagnosis of AMI is the key to reduce mortality and improve prognosis of patients.^[3]^

In the previous clinical diagnosis, AMI was mainly diagnosed based on medical history, physical examination, electrocardiogram, echocardiography and other examinations, but all of these examinations had certain defects and their accuracy was not high, while myocardial necrosis markers such as C reactive protein (CRP), myoglobin (Mb), creatine kinase isoenzyme (CK-MB) have poor sensitivity and specificity in the early stage of the disease.^[4]^ Although cardiac troponin (cTn) has become a recognized indicator for the diagnosis of AMI, the blood concentration reflecting myocardial necrosis cannot be detected within 1 hour after the onset of AMI symptoms, and the level of troponin begins to rise 3 to 6 hours after the occurrence of myocardial injury, appearing the “troponin blindness stage”,^[5]^ since cTn lacks sensitivity in the early stages of myocardial injury, it is particularly important to add a marker for rapid diagnostic AMI. Copeptin is a newly discovered marker of myocardial necrosis. Clinical studies have confirmed that copeptin begin to rise in early AMI, earlier than troponin,^[6]^ breaking the “troponin blindness stage” and making up for defects in early atypical changes in electrocardiogram. Early diagnosis and prognosis evaluation of AMI can be carried out quickly.

Some studies have pointed out that although the level of copeptin in AMI patients is significantly increased, because of the lack of specificity, it should not be considered as a single biomarker for the diagnosis of suspected AMI patients.^[7]^ The sensitivity of hypersensitive cardiac troponin (hs-cTn) is higher than that of traditional troponin. At present, the diagnostic value of hs-cTn combined with copeptin in early detection of AMI is not clear. The aim of this study is to investigate the early diagnostic value of hs-cTnT combined with copeptin in early detection of AMI.

## Materials and methods

2

### Study design

2.1

This is a prospective randomized double-blind diagnostic trial to study the accuracy of copeptin combined with hs-cTnT in the diagnosis of early acute myocardial infarction. This study follows the guidelines of Standards for Reporting of Diagnostic Accuracy Studies,^[8]^ And we followed the Consolidated Standards of Reporting Trials (CONSORT) guidelines for reporting randomized trials and provided a CONSORT flow diagram (Fig. 1).

**Figure 1 F1:**
[figure not shown]
Flow diagram.

### Ethics and registration

2.2

This protocol is in accordance with Helsinki Declaration and approved by the Clinical Research Ethics Committee of our hospital. This experiment has been registered in open science framework (OSF) (Registration number: DOI 10.17605/OSF.IO/6TE5Z). Prior to the trial, written informed consent will be obtained from all patients. Personal information about potential participants and registered participants will be collected, Shared, and kept in a separate repository to protect confidentiality before, during, and after the trial.

### Sample size

2.3

Estimation of sample contents for both test and control groups will be obtained based on anticipated sensitivity according to Buderer formula:^[9,10]^$$n=\frac{Z_{1-\frac{a}{2}}^{2}\times S_{N}\times \left(1-S_{N}\right)}{L^{2}\times Prevalence}$$

Where n = required sample size; S_N_ = anticipated sensitivity; *α* = size of the critical region (1 – α is the confidence level); Z_1-α/2_ = standard normal deviate corresponding to the specified size of the critical region (α), and L = absolute precision desired on either side (half-width of the confidence interval) of sensitivity or specificity. According to the sensitivity of the test group to be 90% and that of the control group to be 75%, the sensitivity of the control group to be 0.8, α=0.05, Z_1-α/2_ = 1.96, L = 0.1, it is calculated that at least 43 persons are required to be included on the test group and 90 persons on the control group. At last, 90 persons are selected from the test group and the control group respectively.

### Patients

2.4

Inclusion criteria: Clinical examination meets the diagnostic criteria of AMI^[11]^; Regardless of gender, age ≥18; Be to the hospital within 2 hours after onset of chest pain; Be all received AMI therapy for the first time and had no old myocardial infarction; Voluntary participants with informed consent of patients and their families.

Exclusion criteria:

1.Patients with severe arrhythmia;2.Patients with congenital heart disease and heart valve organic lesions;3.Patients with malignant tumors examined;4.Patients with heart, liver and kidney dysfunction;5.Unable to understand the research programme or unwilling participants.

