### Statistical analysis

2.8

SPSS 25.0 was used for statistical analysis of the data and normality test of the measurement data. The normal distribution data were expressed as $\bar{x}\pm S$, and the comparison between groups was performed by one-way ANOVA. Non-normal distribution data were represented by median and quartile, rank sum test was used for comparison between groups, Chi-Squared test was used for comparison between count data sets. Receiver operating characteristic curve (ROC) was used to screen the best diagnostic critical point value, and its sensitivity and specificity were calculated to evaluate the diagnostic effect. The area under the 2 ROC curves (AUC) was compared by *Z* test. *P* < .05 was statistically significant.

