## Discussion

3

Since chest pain and other symptoms account for about 5% to 10% of the total number of emergency patients,^[14]^ accurate diagnosis of AMI in chest pain patients in the early stage is of great clinical value in improving the prognosis of patients and reducing their mortality.

Troponin T is a regulatory protein for myocardial tissue contraction and a biochemical marker of myocardial injury and necrosis. It is usually detected from the blood 4 to 6 hours after chest pain occurs. Traditional cTnT detection methods have lower sensitivity and affect the early diagnosis of AMI, while hs-cTnT have higher sensitivity than traditional detection methods.^[15]^ Hs-cTnT has high sensitivity to myocardial injury and strong specificity, can appear in the early stage of AMI, and can exist in the blood stream for a long period of time. It is the most favorable marker for early diagnosis and prognosis evaluation of AMI.^[16]^ The hypersensitive troponin will rise abnormally when there is damage of cardiomyocytes and the sensitivity is high, serum level of hypersensitive troponin T is positively correlated with the degree of myocardial injury in acute myocardial infarction.^[17]^

Copeptin, a part of the original C-terminal of arginine vasopressin (AVP), is positively correlated with AVP in the normal population and patients with cardiopulmonary and vascular diseases, and is an acute endogenous stress marker. Its stability in vivo is stronger than AVP, and it is easy to measure. Therefore, copeptin can replace AVP as a clinical early-warning marker of cardiovascular disease.^[18]^ The plasma copeptin level peaks immediately after AMI, and decreases gradually within 6 hours, with the largest change range within 0 to 3 hours.^[19]^ However, the copeptin specificity is low, and it can increase in acute or chronic stress state, such as respiratory tract infection, chronic obstructive pulmonary disease, heart failure, critical illness and so on, which has certain influence on the early diagnosis of AMI.^[20]^ The combination of copeptin and hs-cTnT detection is expected to improve specificity and accuracy in early diagnosis of acute myocardial infarction.

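### Entry requires that the AMI criteria are already met, yet specificity, an ROC cut-off and an AUC test are planned, and the sample size implies non-AMI patients whom the entry rule does not admit

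*Protocol article*

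**What the plan says.** **Who enters.** The first inclusion criterion in Section 2.4 (Patients) is "Clinical examination meets the diagnostic criteria of AMI". A later one reads "Be all received AMI therapy for the first time and had no old myocardial infarction". Arrival must be within 2 hours of the onset of chest pain. Section 2.5 randomises these patients 1:1 to copeptin plus hs-cTnT or to cTnI. Both groups therefore come from the same population, and neither is a disease-free control.

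**What is to be estimated.** The Abstract (Methods) promises a comparison of sensitivity at different time periods and "the sensitivity and specificity comparison of the two detection methods". Section 2.8 (Statistical analysis) says that an ROC curve "was used to screen the best diagnostic critical point value, and its sensitivity and specificity were calculated to evaluate the diagnostic effect". It adds: "The area under the 2 ROC curves (AUC) was compared by" a Z test.

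**How disease status is verified.** Section 2.6 (Methods) has every patient undergo coronary angiography as the gold standard. It describes the technique but not which finding counts as AMI and which as non-AMI.

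**How the trial was sized.** Section 2.3 uses the Buderer formula for sensitivity, which has prevalence in the denominator. It gives sensitivities of 90% (test) and 75% (control), a second control-group sensitivity of 0.8, α = 0.05 and L = 0.1. It reports minima of 43 and 90 and settles on 90 per group. No value is labelled as prevalence.

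**The concern.** Specificity is the proportion of non-AMI patients with a negative test. The horizontal axis of an ROC curve is the false-positive proportion in those same patients, and the AUC compares marker values between patients with and without disease. If everyone enrolled has AMI, none of the three exists. Sensitivity remains estimable, including sensitivity by time point, which the Abstract lists first.

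Specificity is not a side issue here. The Introduction says that copeptin's lack of specificity stops it from serving as a single marker, and the Discussion expects the combination to improve specificity. An entry rule that leaves out non-AMI patients leaves that expectation untested. The sample size, meanwhile, appears to assume that such patients will be present.

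**Working it through.** **1. Reproduce the stated sample size.** From Section 2.3: n = Z² × SN × (1 − SN) / (L² × Prevalence), with Z = 1.96 (Z² = 3.8416) and L = 0.1 (L² = 0.01). Try the unexplained 0.8 as the prevalence:

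- Test group, SN = 0.90: 3.8416 × 0.09 / (0.01 × 0.8) = 43.2. Stated: 43.
- Control group, SN = 0.75: 3.8416 × 0.1875 / (0.01 × 0.8) = 90.04. Stated: 90.

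Both figures reproduce, to the nearest whole number.

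**2. Try the other readings.**

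- Prevalence 1.0, as the entry rule implies: 3.8416 × 0.09 / 0.01 = 34.6 and 3.8416 × 0.1875 / 0.01 = 72.0. Neither matches.
- 0.8 as the control-group sensitivity, as labelled: 3.8416 × 0.16 / 0.01 = 61.5 at prevalence 1.0, or 76.8 at prevalence 0.8. Neither gives 90.

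So 0.8 acts as the prevalence.

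**3. Count the non-AMI patients per group of 90.**

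- Entry rule read literally (prevalence 1.0): 90 × 0 = 0. Specificity is 0/0, and there is no ROC curve or AUC.
- Prevalence implied by Section 2.3 (0.8): 90 × 0.2 = 18.

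**4. Precision of specificity with 18 negatives.** The half-width is 1.96 × √(Sp × (1 − Sp) / 18). The article gives no anticipated specificity, so 0.90 and 0.80 are assumptions.

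- Sp = 0.90: 1.96 × √(0.09 / 18) = 0.139.
- Sp = 0.80: 1.96 × √(0.16 / 18) = 0.185.

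Section 2.3 defines L as the half-width for sensitivity or specificity and sets it at 0.1. At prevalence 0.8, reaching 0.1 for specificity would need 3.8416 × 0.09 / (0.01 × 0.2) = 173 patients per group (Sp 0.90) or 3.8416 × 0.16 / (0.01 × 0.2) = 307 (Sp 0.80).

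**5. Precision of sensitivity if all 90 have AMI.**

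- SN = 0.90: 1.96 × √(0.09 / 90) = 0.06.
- SN = 0.75: 1.96 × √(0.1875 / 90) = 0.09.

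Both are within the stated 0.1.

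**6. Precision if entry is widened to suspected AMI, still 90 per group.** Same half-width formula, with the number of AMI or non-AMI patients as denominator. Prevalences other than 0.8, and both specificities, are assumptions.

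| Prevalence | AMI / non-AMI | SN 0.90 | SN 0.75 | Sp 0.90 | Sp 0.80 |
|---|---|---|---|---|---|
| 0.8 | 72 / 18 | 0.07 | 0.10 | 0.14 | 0.19 |
| 0.5 | 45 / 45 | 0.09 | 0.13 | 0.09 | 0.12 |
| 0.2 | 18 / 72 | 0.14 | 0.20 | 0.07 | 0.09 |

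**The case against.** The strongest reply is that disease status does not rest on the entry criterion. Entry depends on clinical examination, and angiography then validates the diagnosis in everyone. Some enrolled patients could be negative on angiography, and the 0.8 recovered from Section 2.3 suggests that about 20% were expected to be. On that reading specificity can be estimated.

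This stands in part. A reader might infer from Section 2.4 alone that zero negatives is a settled fact. The document does not support that much, because Sections 2.3 and 2.6 leave room for some. But the reply does not rescue the plan. No rule turns an angiogram into AMI or non-AMI. Any negatives would be patients who had already met the AMI criteria, a small and selected set that need not resemble non-AMI patients with chest pain. Eighteen per group also falls short of the stated precision.

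A second reply is that the wording is loose and suspected AMI was meant. The phrase about AMI therapy is indeed garbled and may only mean a first infarction. But eligibility is stated here rather than left to another document, and an analysis plan cannot supply patients whom the entry criteria exclude.

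Two further inferences should be resisted. The article says that copeptin's specificity is low, but does not call this its main weakness. The 2-hour limit governs arrival, not diagnosis, so the text does not show that enrolled patients are diagnosed within 2 hours and hence have the least need of an early marker.

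**Conclusion.** The contradiction is real and must be resolved. Section 2.4 as written admits no non-AMI patients, Section 2.3 implies about 18 per group, Section 2.6 does not say how any would be identified, and the Abstract and Section 2.8 plan three analyses that depend on them. Followed literally, the plan can deliver sensitivity only. On its most generous reading, specificity rests on about 18 selected patients per group, with a half-width of about 0.14 to 0.19 where 0.1 was specified.

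The figure of 18 assumes that 0.8 is the prevalence, which is the only reading found to reproduce both 43 and 90. The half-widths assume specificities of 0.90 and 0.80, because the article gives none.

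The exclusion "Patients with heart, liver and kidney dysfunction" is a separate matter. The Discussion names heart failure among the causes of raised copeptin, so this exclusion would limit how far any specificity result generalises. It has no bearing on whether specificity can be estimated.

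**What to change.** Reconcile the Abstract with Sections 2.3, 2.4, 2.6 and 2.8, by one of two routes. Either way, label the 0.8 in Section 2.3 for what it is.

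**Option 1: keep the AMI population.** Delete specificity, ROC cut-off selection and the AUC test from the objectives and analysis. Limit the conclusion to sensitivity, overall and by time point, in patients meeting the AMI criteria. Restate the sample size without the 0.8. This changes wording only, and 90 per group still meets L = 0.1 for both anticipated sensitivities. The price is a narrower conclusion: nothing could be said about specificity or about diagnosis among patients with suspected AMI.

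**Option 2: widen entry.** Enrol patients with suspected AMI before the diagnosis is confirmed or excluded. Define AMI and non-AMI by a reference standard that does not use the study markers and is reconciled with angiography in Section 2.6. Restate the precision for both sensitivity and specificity at the expected prevalence. This preserves the stated aims but is not free. The reference standard, at present invasive angiography for all, must be applied to or redefined for non-AMI patients. Precision for sensitivity also falls: at an assumed prevalence of 20%, 18 AMI patients per group give half-widths of about 0.14 (sensitivity 0.90) and 0.20 (0.75), so the trial would have to grow or accept wider intervals.

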### Methods

2.6

1.After admission, 5 ml cubital venous blood was collected from all patients at 0 hours, 4 hours and 6 hours, respectively. According to the digital markers assigned at admission, the blood was centrifuged at 3000 r/minutes for 10 minutes, and the plasma was collected and stored at -70°C for testing.2.cTnI detection: Immunofluorescence assay was used, the kit was produced by Roche in Germany, cTnI value <0.05ng/ml was used as the diagnostic cut-off point; (2) hs-cTnT detection: Electrochemical luminescence method was used on roche Cobas 601 automatic chemiluminescence instrument. The kit was Roche fifth generation trotropoin reagent, and hs-cTnT value ≤14 ng/L as the diagnostic cut-off point^[12]^; (3) copeptin detection: Using enzyme linked immunosorbent assay (ELISA), the kit was produced by phoenix pharmaceuticals in the United States, and the copeptin value <14 pmol/L as the diagnostic cut-off point.^[6,13]^3.All patients underwent coronary angiography as the gold standard for diagnostic validation: CAG was performed by an experienced interventional cardiologist using the standard Judkins method, with at least 3 multi-position exposures per vessel.

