Cardiac troponin I remains the preferred cardiac marker for AMI diagnosis, according to guidelines published by the European Society of Cardiology (ESC), the American College of Cardiology (ACC), and the American Heart Association (AHA).^[21,22]^ Therefore, we used cTnI as a control group to evaluate the clinical value of copeptin combined hs-cTnT in the diagnosis of early acute myocardial infarction.

This study may have the following limitations: because this is a single central regional experimental study, the inclusion of the population may be relatively single, there is a certain bias; factors such as age may have a certain impact on the results.

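### Entry requires AMI criteria that are not spelled out; if a clinical troponin result helps to meet them, sensitivity is overstated by selection at entry, plausibly more for the cTnI comparator

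*Protocol article*

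**What the plan says.** The inclusion criteria (protocol article, section 2.4, Patients) require that "Clinical examination meets the diagnostic criteria of AMI". A reference number stands in place of the criteria themselves. The same list adds "Be all received AMI therapy for the first time and had no old myocardial infarction" and "Be to the hospital within 2 hours after onset of chest pain". Enrolled patients therefore already carry the AMI label.

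On what that label usually rests, the Introduction says that "cardiac troponin (cTn) has become a recognized indicator for the diagnosis of AMI". It also describes the older approach: "AMI was mainly diagnosed based on medical history, physical examination, electrocardiogram, echocardiography and other examinations". The Discussion says that "Cardiac troponin I remains the preferred cardiac marker for AMI diagnosis" and gives this as the reason for choosing cTnI as the control test.

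Section 2.6 (Methods) takes blood at 0, 4 and 6 hours after admission, and "the plasma was collected and stored at -70°C for testing". On the reference standard it says: "All patients underwent coronary angiography as the gold standard for diagnostic validation".

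**The concern.** The trial asks whether copeptin with hs-cTnT detects early AMI that cTnI misses. The Introduction motivates this by the early period in which troponin has not yet risen. The patients who matter most are therefore those with AMI and a negative troponin.

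An entry rule that requires AMI criteria to be met already can work against this group. Suppose a clinical troponin result is one of the ways to meet the criteria. A patient with raised troponin then enters. A patient with AMI but no raised troponin enters only if the ECG or other findings suffice. Patients who fail on both are lost, and they are false negatives of the comparator. Losing them raises the observed sensitivity.

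Sensitivity is the quantity used for the sample size (section 2.3) and the first stated focus of the abstract. The effect is also separate from the shortage of non-AMI patients: adding controls would help specificity and the ROC analysis but would leave the sensitivities selected.

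**Working it through.** **1. The plan's own figure.** Section 2.3 uses n = Z² × S × (1 − S) / (L² × prevalence), with Z = 1.96 and L = 0.1. Anticipated sensitivities are 0.90 (test) and 0.75 (control). A further value of 0.8 is printed as a second control-group sensitivity.

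- Test: 3.8416 × 0.90 × 0.10 / (0.01 × 0.8) = 43.22; the plan states 43.
- Control: 3.8416 × 0.75 × 0.25 / (0.01 × 0.8) = 90.04; the plan states 90.

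The figures reproduce (strict rounding up gives 44 and 91), but only if 0.8 is read as prevalence. On that reading the sizing expects 90 × 0.8 = 72 AMI patients and 18 others per group. The entry rule, taken literally, implies a prevalence of 1, for which the formula gives 34.57 and 72.03. None of this measures the selection effect, but it shows that the sizing already assumes a mixed cohort.

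**2. Selection at entry, cTnI.** Let s be the true cTnI sensitivity among AMI patients who present. Let q be the share who can enter only when cTnI is positive, taken as the same in cTnI-positive and cTnI-negative patients. All positives enter (s). Of the negatives, (1 − s)(1 − q) enter. So

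observed sensitivity = s / (s + (1 − s)(1 − q)).

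With s = 0.75:
- q = 0.25: 0.75 / (0.75 + 0.25 × 0.75) = 0.75 / 0.9375 = 0.800
- q = 0.50: 0.75 / (0.75 + 0.25 × 0.50) = 0.75 / 0.875 = 0.857

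**3. The combination.** The article does not state how copeptin and hs-cTnT are combined, so two assumptions are shown, both with a true sensitivity of 0.90. If every cTnI-positive patient is also combination-positive (nested), observed sensitivity is (0.75 + 0.15(1 − q)) / (0.75 + 0.25(1 − q)). If the tests are independent given AMI, it stays at 0.90.

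| q (assumed) | cTnI | Combination, nested | Difference, nested | Difference, independent |
|---|---|---|---|---|
| 0 | 0.750 | 0.900 | 0.150 | 0.150 |
| 0.10 | 0.769 | 0.908 | 0.138 | 0.131 |
| 0.25 | 0.800 | 0.920 | 0.120 | 0.100 |
| 0.50 | 0.857 | 0.943 | 0.086 | 0.043 |

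Differences are taken before rounding. In each row with q > 0, cTnI gains more than the combination. At q = 0 nothing changes.

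**4. Why q, and not the share of entrants with a positive troponin, is the right quantity.** Take 100 AMI patients, 75 of them cTnI-positive. Suppose 40 qualify through troponin, and every other patient, including all 25 negatives, qualifies on other findings. Observed sensitivity is still 75/100 = 0.75, so there is no bias although 40% entered on troponin. Among the other 60 patients it is 35/60 = 0.583. The bias comes from patients left out, not from the route taken by those let in.

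**The case against.** The strongest objection is that the article never says its entry criteria use troponin. A reader might infer from the Introduction and Discussion that they do, but those are general remarks about practice. The criterion speaks of clinical examination, the cited source is not shown, and a condensed article may leave the detail to the full protocol. This stands, and it makes the point conditional.

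A reader might also call this incorporation bias. The documents do not support that term in its usual sense: the declared reference standard is angiography, and the study's plasma is frozen for later testing, so the study's own assays are unlikely to have decided entry. What these facts do not exclude is a separate clinical troponin result acting at entry. Nor can angiography restore patients who were never enrolled.

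Timing weakens the mechanism. Patients arrive within 2 hours, numbers are assigned at admission, and the article puts the troponin rise at 3 to 6 hours. On those figures few patients would qualify through troponin on arrival. This stands in part: the article does not say when the criteria must be judged met.

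It is tempting to state as fact that both sensitivities are inflated, most for cTnI, and to turn this into a loss of power. The ordering depends on which troponin is used clinically (hs-cTnT is one too) and on how the two markers are combined. The sample size rests on precision (L = 0.1), not on detecting a difference, so there is no planned power to lose.

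**Conclusion.** The concern holds as a conditional risk. Entry requires an AMI diagnosis whose criteria are not spelled out, in an article that presents the comparator as the preferred marker for that diagnosis. If a clinical troponin result contributes to entry, early troponin-negative AMI patients can drop out of the denominator and sensitivity is overstated by selection.

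The size cannot be fixed, because q is not in the documents. With the planned 0.75, observed cTnI sensitivity runs from 0.75 (q = 0) through 0.80 (q = 0.25) and 0.857 (q = 0.5) to 1.00 (q = 1). At q = 0.5 the planned 15-point contrast would be 8.6 points (nested) or 4.3 points (independent). These figures assume that cTnI is the troponin used at entry and that q does not depend on cTnI status. That cTnI gains more is plausible, not established.

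**What to change.** In section 2.4, replace the confirmed-AMI criterion with suspected AMI on presentation: chest pain within 2 hours, with clinical and ECG findings. State that no troponin or copeptin result is used for entry. Record the basis of entry for each patient. The clause on AMI therapy in the same list must be reconciled with the new wording.

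Limiting the main comparison to patients whose entry did not rest on troponin would not be a remedy. It removes patients already known to be troponin-positive and so biases against cTnI, as the 0.583 in the example shows.

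The cost is a change to the eligibility wording and one case-report-form field. The target population becomes suspected rather than confirmed AMI, and some entrants will not have it. The 0.8 in section 2.3, if read as prevalence, already allows for that. If troponin never played a part in entry, a sentence saying so, with the criteria spelled out, would settle the matter.
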